## Abstract

**Background:**

Axillary lymph node dissection (ALND) in patients with breast cancer has the potential to induce side-effects, including upper-limb lymphedema. Axillary reverse mapping (ARM) is a technique that enables discrimination of the lymphatic drainage of the breast from that of the upper limb in the axillary lymph node (LN) basin. If lymphedema is caused by removing these lymphatics and nodes in the upper limb, the possibility of identifying these lymphatics would enable surgeons to preserve them. The aim of this study is to determine the clinical relevance of selective axillary LN and lymphatic preservation by means of ARM. To minimize the risk of overlooking tumor-positive ARM nodes and the associated risk of undertreatment, we will only include patients with a tumor-positive sentinel lymph node (SLN). Patients who are candidates for ALND because of a proven positive axillary LN at clinical examination can be included in a registration study.

**Methods/design:**

The study will enroll 280 patients diagnosed with SLN biopsy-proven metastasis of invasive breast cancer with an indication for a completion ALND. Patients will be randomized to undergo standard ALND or an ALND in which the ARM nodes and their corresponding lymphatics will be left *in situ*. Primary outcome is the presence of axillary surgery-related lymphedema at 6, 12, and 24 months post-operatively, measured by the water-displacement method. Secondary outcome measures include pain, paresthesia, numbness, and loss of shoulder mobility, quality of life, and axillary recurrence risk.

**Discussion:**

The benefit of ALND in patients with a positive SLN is a subject of debate. For many patients, an ALND will remain the treatment of choice. This multicenter randomized trial will provide evidence of whether or not axillary LN preservation by means of ARM decreases the side-effects of an ALND. Enrolment of patients will start in April 2013 in five breast-cancer centers in the Netherlands, and is expected to conclude by April 2016.

**Trial registration:**

TC3698

## Background

Axillary lymph node dissection (ALND) for patients with breast cancer has the potential to cause side-effects, including pain, numbness or paresthesia, arm/shoulder mobility restriction, and lymphedema [1]. Arm lymphedema has been documented in 7 to 77% of patients who undergo ALND [2,3]. The incidence of lymphedema depends on whether ALND has been combined with subsequent radiotherapy, but also on the definition of ALND used.

Sentinel lymph node biopsy (SLNB) represents the standard of care for axillary node staging in patients with early-stage, clinically node-negative breast cancer (cT1 to 2N0). The goals of SLNB are to reduce the morbidity from breast-cancer surgery by avoiding unnecessary ALND and to improve staging of the regional LNs. However, in a selected group of patients, ALND is still indicated.

Axillary reverse mapping (ARM) is a recently developed technique that enables surgeons to discriminate the lymphatic drainage pattern of the breast from that of the upper limb. The concept of ARM is to map the drainage of the upper limb to determine the anatomical variation in these lymphatics and thus create a road map for their preservation. If lymphedema is caused by removing the lymphatics and nodes of the upper limb, the possibility of identifying these lymphatics would enable surgeons to preserve them [4]. The ARM technique can be performed by using blue dye, fluorescent dye, or a radioisotope. In the past few years, several groups have reported their first experiences with this relatively new technique [5-13]. A review by Ngochi on this topic [14] clearly described the ARM techniques that are currently available. Studies on ARM using blue dye reported identification rates varying between 50 and 89% [5-10], and for isotope and fluorescent dyes, these rates are 91 to 100% [11,13] and 88% [12] respectively. The latter two visualization techniques have the advantage of not leaving a ‘blue tattoo’ on the patient’s skin. However, there is limited information on the use of isotopes and fluorescent dyes, and they require the use of expensive equipment during surgery.

Despite these promising results, there are some problems that need to be considered before ARM can be used in routine clinical practice. The currently available techniques are insufficient to identity the upper-limb LNs in some patients. The relevance of the ARM procedure is based on the assumption that the lymphatic pathways from the upper limb are not involved in metastasis of the primary breast cancer [5]; however, in a minority of patients, the SLN draining of the breast may be the same as the ARM node draining the upper limb. This may explain why the ARM nodes may be involved with metastatic foci in patients with clinically axillary LN metastases. These issues may represent an important drawback for the implementation of the ARM procedure.

Boneti *et al*. recently published a phase II trial of ARM with promising results [16]. The study showed that preserving the ARM nodes in a clinically negative axilla is safe, and results in a low incidence of post-operative lymphedema in patients undergoing ALND and SLNB. However, further studies are needed before this technique can be adopted as a standard procedure during complementary ALND (cALND) in the surgical treatment of breast cancer.

In this paper, we present the design for a multicenter randomized controlled trial to determine the clinical relevance and safety of selectively sparing upper-limb axillary LNs and their corresponding lymphatics by means of ARM. To minimize the risk of under-treatment due to non-removal of possible ARM node metastases, we will only include patients based on a tumor-positive SLN.

## Methods/design

The aim of the ARM trial is to determine the usefulness of the ARM technique in identifying and sparing the upper limb-related axillary LNs, and its ability to reduce the risk of lymphedema of the upper limb. After determining the indication for a cALND basis on a tumor-positive SLN, patients will be randomly allocated to one of two groups: ALND with preservation of the upper limb-related axillary LNs (ARM-ALND) and a level I-II ALND (standard ALND).

Patients who are candidates for a primary axillary lymph node dissection (pALND), based on axillary metastases proven by pre-operative cytology, can be included in the registration study to confirm the feasibility of the procedure and to perform a further subgroup analysis. A schematic overview of the trial is given in Figure 1.

**Figure 1 F1:**
[figure not shown]
**Flow chart of axillary reverse mapping (ARM) trial. **ALND, Axillary lymph node dissection; cALND, complementary axillary lymph node dissection based on a tumor-positive sentinel node; pALND, primary axillary lymph node dissection based on a tumor-positive axilla proven by pre-operative cytology; ARM-ALND axillary lymph node dissection with preservation of the upper limb-related axillary lymph nodes; standard ALND, level I-II axillary lymph node dissection.

### Participants

Female patients aged over 18 years presenting with invasive breast cancer and an indication for a cALND based on a positive SLN will be deemed eligible for the trial. The indication for the ALND should be made by a multidisciplinary team including an oncologic surgeon, a medical oncologist, a pathologist, a radiologist, and a radiotherapist. Informed consent will be obtained from all patients. Exclusion criteria are: indication for pALND based on a clinical positive axilla; contraindication for SLNB; an adverse event during the previous SLNB; history of breast cancer or axillary surgery; or pregnancy.

Patients who undergo an ALND based on a clinically positive axilla can participate in the registration study, in which patients will undergo ARM during ALND. In this group of patients, no attempt will be made to spare LNs or lymphatics.

### Objectives

The hypothesis is that patients undergoing ARM-ALND will have fewer post-operative complications than patients undergoing standard ALND. The post-operative complications that will be measured are the occurrence of breast cancer-related lymphedema (BCRL) and paresthesia/numbness, pain, and shoulder immobility. The hypothesis is that a reduction in the risk of post-operative complications in patients undergoing ARM-ALND will result in a better quality of life compared with those undergoing standard ALND. Based on the results of our feasibility study, in which no LN metastasis where found in the patients with tumor-positive SLN, it is expected that the axillary recurrence risk in the ARM-ALND group will be comparable with the risk in the standard ALND group.

#### Research question

1. Will there be fewer post-operative complications after ARM-ALND compared with standard ALND in patients with an indication for a cALND based on a positive SLNB? Post-operative complications are expected to include the following. primary complication: BCRL; secondary: pain, paresthesia/numbness, and loss of shoulder mobility.

2. Will the possible reductions in these post-operative complications have a positive effect on the quality of life (QoL)?

3. Will patients undergoing ARM-ALND have a similar risk of axillary recurrence as the patients undergoing standard ALND?

### Randomization

Randomization will be performed using a web-based randomization system, and will be stratified by center. This randomization application and the internet-based help service will be available 24 hours a day, 7 days a week. Because of practical considerations, the randomization will take place as soon as the patient has given written informed consent. Based on our previous experience with the ARM procedure, we expect that identification or preservation of the ARM nodes/lymphatics will not be possible in 5 to 15% of the randomized patients. In such cases, the standard ALND will be performed, if possible, and the ARM nodes/lymphatics will be separately removed and sent for analysis. These patients will be included in the analysis in accordance with the intention-to-treat principle, but excluded from the sensitivity analysis. (Figure 1) (more information can be found at http://www.armstudie.nl).

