### Interventions

Surgeons familiar with the ARM procedure will perform the ALND. In our feasibility study (Amphia Hospital Breda, the Netherlands), the learning curve for performing the ARM procedure was very small (barely measureable), and the overall identification rate of the upper-limb LNs was up to 94%. Based on these results, we consider an oncologic breast surgeon should be capable of performing an ARM procedure once they have performed five procedures under the supervision of one of the oncologic surgeons (EL or PG) from the Amphia Hospital Breda.

The procedure will be performed under general anesthesia. For the procedure, approximately 2 ml of blue patent V dye (Laboratoire Guerbet, Aulnay-sous-Bois, France) from a stock solution of 25 mg/ml is injected subcutaneously into the inner arm, along the medial intermuscular groove of the ipsilateral arm. This dye is identical to the dye used to perform an SLNB. After injection, the site of injection is massaged and the arm elevated for a few minutes to enhance lymphatic drainage of this limb. Next, the patient is covered with sterile drapes, and the ALND can be started.

The technical part of the operation is identical to a normal level I to II ALND, except for the first part of the operation. After incision, the blue-stained LNs and lymphatics are identified. In the ARM-ALND group, the blue-stained LNs and lymphatics will be spared, then a normal ALND will be performed. In the standard ALND group, a normal ALND will be performed without sparing the upper-limb lymphatics and LNs. The pathologist will separately analyze the LNs (level I to II nodes and ARM nodes, Figure 2).

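### The sensitivity analysis excludes patients on an intra-operative event that is at least partly specific to the ARM-ALND arm, so it is not a randomized comparison and could be biased in either direction

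*Protocol article*

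**What the plan says.** Under Randomization, the protocol article states that "the randomization will take place as soon as the patient has given written informed consent", which is before surgery. It goes on: "we expect that identification or preservation of the ARM nodes/lymphatics will not be possible in 5 to 15% of the randomized patients". For these patients, "In such cases, the standard ALND will be performed, if possible, and the ARM nodes/lymphatics will be separately removed and sent for analysis". Their place in the analysis is then fixed: "These patients will be included in the analysis in accordance with the intention-to-treat principle, but excluded from the sensitivity analysis". No arm is named.

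Under Interventions, mapping is described before the two arms separate: "After incision, the blue-stained LNs and lymphatics are identified". The arms then differ. In one, "In the ARM-ALND group, the blue-stained LNs and lymphatics will be spared, then a normal ALND will be performed". In the other, "In the standard ALND group, a normal ALND will be performed without sparing the upper-limb lymphatics and LNs".

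The Blinding section says that the surgeon cannot be blinded, and Data collection makes the operating surgeon responsible for the peri-operative data.

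**The concern.** A sensitivity analysis should show whether the intention-to-treat result survives a reasonable change of assumption. This one drops patients because of something that happens during the operation, after allocation, and the criterion does not mean the same thing in the two arms.

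- **Preservation.** It is attempted in only one arm, so it can fail in only one arm. Standard-arm patients whose nodes would also have been impossible to spare stay in the analysis.
- **Identification.** It can fail in either arm. However, the surgeon knows the allocation, needs the blue nodes for sparing in only one arm, and records the event that decides exclusion. Identification failures may not be comparable between arms even if the rule is applied to both.

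If the excluded patients differ from the rest in their underlying risk of lymphedema, the restricted comparison will show a difference that the treatment did not cause.

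**Working it through.** **The plan's own figure.** Sample size gives 15% v 5%, power 0.80, type I error 0.05 and 140 per arm. The two-sided two-proportion formula with pooled variance and no continuity correction gives 141 per arm, and 140 per arm gives power 0.800. The figure reproduces, so 15%, the 10-point effect and 140 per arm are used below.

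**Inputs**
- Control risk: 15% (Sample size).
- Share with failed identification or preservation, f: 5 to 15% (Randomization).
- Risk of excluded relative to kept patients, r: not given in the document. The range 0.5 to 3 is an assumption.

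**Case 1: exclusion from the ARM-ALND arm only, no true effect.** Overall risk in that arm is 0.15 = f × r × p + (1 − f) × p, where p is the risk among those kept. Hence p = 0.15 / (1 − f + f × r), and the false difference is 0.15 − p. For example, with f = 0.15 and r = 3, p = 0.15 / 1.30 = 0.1154, a difference of 3.5 points.

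False difference in percentage points (positive favours ARM):

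| f | Kept in ARM-ALND arm | r = 0.5 | r = 1 | r = 2 | r = 3 |
|---|---|---|---|---|---|
| 5% | 133 | −0.4 | 0 | 0.7 | 1.4 |
| 10% | 126 | −0.8 | 0 | 1.4 | 2.5 |
| 15% | 119 | −1.2 | 0 | 2.0 | 3.5 |

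At f = 15% (140 v 119 patients, normal approximation), the chance of a false significant result in favour of ARM, nominally 2.5%, is 1.3% for r = 0.5, 6.5% for r = 2 and 12.4% for r = 3.

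**Case 2: identification failures dropped from both arms.** If identification fails equally often and in similar patients in each arm, that part of the selection cancels and only preservation failures remain one-sided. The document gives no figure for them. If they are 1 to 2% (an assumption) with r = 3, then p = 0.15 / 1.02 = 0.1471 to 0.15 / 1.04 = 0.1442, a false difference of 0.3 to 0.6 points.

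**Dilution is a separate matter.** If failed patients in the ARM-ALND arm carry the 15% standard risk, the intention-to-treat risk there is (1 − f) × 5% + f × 15%, which is 5.5% to 6.5%. A larger difference after exclusion is therefore partly the removal of dilution, which is not in itself bias. The restricted analysis cannot separate the two.

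**The alternative in the same settings.** The complier-average effect is the intention-to-treat difference divided by the proportion preserved.
- With no true effect it is 0 / (1 − f) = 0, whatever r is.
- With the planned effect, 10% failures and 15% risk in those failures under either allocation, the intention-to-treat difference is 15% − 6% = 9 points, and 9 / 0.90 = 10 points. The planned effect is recovered.

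**The case against.** A reader might infer that the exclusion can occur only in the ARM-ALND arm and that it must favour ARM. The document does not support either statement.

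- The rule covers identification as well as preservation and refers to randomized patients in general. Mapping is described before the arms separate, so failed identification may be recorded in the standard arm too. The fallback to standard ALND is a change of treatment only for ARM-ALND patients, which hints at a one-arm reading but does not settle it.
- No lymphedema risk is given for the excluded patients. The bias is zero at r = 1 and reverses below 1. The idea that failures cluster in more involved axillae is plausible but unsupported. In the pilot described under Background, visualization was 86% in the sentinel-node-positive group and 94% in the cytology-proven group (P = 0.196), which if anything points the other way for identification.
- Those pilot rates imply 14% and 6% non-identification, nearly the whole of the stated 5 to 15%. The necessarily one-sided part may be small.
- The intention-to-treat analysis keeps everyone, and the article gives the sensitivity analysis no confirmatory role. The exact population for each arm may be set out in the flow chart, which is not shown here, or in the full protocol.

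All of this limits the claim about direction and size. It does not remove the problem. Excluding on failed preservation is a stated rule, it has no counterpart in the standard arm, and following it exactly gives a comparison that randomization does not protect.

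**Conclusion.** The concern holds in a limited form. The sensitivity analysis excludes on a post-randomization criterion. Its preservation part exists in one arm only, and its identification part is judged by an unblinded surgeon with no stated rule on which arms it covers. Balance between the groups cannot be assumed.

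The worst case of 3.5 points is about a third of the planned 10-point effect. It needs all of the following: 15% excluded, exclusion from the ARM-ALND arm alone, and three times the risk in those excluded. The risk ratio is assumed throughout, so neither the sign nor the size of the bias is established. The primary intention-to-treat comparison does not depend on this rule. The point is therefore a correction to a supporting analysis and no threat to the main result.

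**What to change.** Replace the exclusion-based sensitivity analysis, or at least accompany it, with a complier-average causal effect: the intention-to-treat risk difference at 24 months divided by the proportion of the ARM-ALND arm in whom the nodes were preserved, with a bootstrap interval. This suits the design because departures run one way: some ARM-ALND patients receive standard ALND, and sparing is not offered in the standard arm. State the assumption it needs, that patients with failed preservation have the same outcome as they would have had if allocated to standard ALND.

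If the restricted analysis is kept, apply the identification criterion equally in both arms, do not exclude on preservation, say so in the text, and label the result a non-randomized comparison.

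The cost is a change of wording, a little more analysis on data already collected, one added assumption and a wider interval. Dividing by 0.95 to 0.85 widens the intention-to-treat interval by a factor of about 1 / 0.95 = 1.05 to 1 / 0.85 = 1.18, before allowing for estimation of the proportion. Moving randomization into theatre is not proposed: the protocol fixed its timing for practical reasons, and changing it would not be cheap.

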### Interventions

Surgeons familiar with the ARM procedure will perform the ALND. In our feasibility study (Amphia Hospital Breda, the Netherlands), the learning curve for performing the ARM procedure was very small (barely measureable), and the overall identification rate of the upper-limb LNs was up to 94%. Based on these results, we consider an oncologic breast surgeon should be capable of performing an ARM procedure once they have performed five procedures under the supervision of one of the oncologic surgeons (EL or PG) from the Amphia Hospital Breda.

The procedure will be performed under general anesthesia. For the procedure, approximately 2 ml of blue patent V dye (Laboratoire Guerbet, Aulnay-sous-Bois, France) from a stock solution of 25 mg/ml is injected subcutaneously into the inner arm, along the medial intermuscular groove of the ipsilateral arm. This dye is identical to the dye used to perform an SLNB. After injection, the site of injection is massaged and the arm elevated for a few minutes to enhance lymphatic drainage of this limb. Next, the patient is covered with sterile drapes, and the ALND can be started.

The technical part of the operation is identical to a normal level I to II ALND, except for the first part of the operation. After incision, the blue-stained LNs and lymphatics are identified. In the ARM-ALND group, the blue-stained LNs and lymphatics will be spared, then a normal ALND will be performed. In the standard ALND group, a normal ALND will be performed without sparing the upper-limb lymphatics and LNs. The pathologist will separately analyze the LNs (level I to II nodes and ARM nodes, Figure 2).

**Figure 2 F2:**
[figure not shown]
Axillary reverse mapping (ARM) procedure.

### Settings and location

The study is a multicenter randomized controlled trial, which will be conducted in the Netherlands. Already five dedicated breast-cancer centers in the Netherlands are willing to participate. These are: Amphia Hospital, Breda; Catharina Hospital, Eindhoven; Haga Hospital, The Hague; Hospital Gelderse Vallei, Ede; and Albert Schweitzer Hospital, Dordrecht.

Patients eligible for inclusion will be enrolled by the breast surgeon at the outpatient clinic, after providing informed consent.

### Primary and secondary outcome measures

The primary outcome will be the occurrence of lymphedema in the upper limb. Lymphedema will be measured s at 6, 12 and 24 months, using the following two techniques.

1) The water-displacement method. This method is regarded as the gold standard for the measurement of lymphedema. For the assessment of upper-limb volume, an arm volume meter will be used (NV Varitex Haarlem, The Netherlands). This method has high reproducibility [17]. Both upper limbs will be measured pre-operatively and post-operatively. Lymphedema is defined as a difference in limb volume of greater than 200 ml between the treated and untreated side, as described by Lopez Penha *et al*. [18].

2) Circumference method. The arm circumference will be measured at four sites: metacarpophalangeal joints, wrist, 100 mm distal from the lateral epicondyle, and 150 mm proximal of the epicondyle. A difference of more than 20 mm between the affected and contralateral arm is considered clinically significant.

The secondary endpoints will be measured at 6, 12, and 24 months and comprise the following:

1) Paresthesia/numbness. This will be assessed with the aid of a standardized questionnaire developed for patients with breast cancer [19].

2) Pain. This will be measured using a visual analog scale.

3) Loss of shoulder mobility. The shoulder function of the affected upper limb will be compared with the unaffected one. Loss of abduction of more than 20 degrees will be considered abnormal.

4) Quality of life. This will be assessed by a standardized questionnaire developed for patients with breast cancer [21]. This large questionnaire includes the WHOQOL-Bref.

5) Locoregional recurrence rate: This will be assessed by a physical examination during follow-up. In cases where there is suspicion of recurrence, ultrasonography (with or without biopsy) will be performed.

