### Data collection

A nurse practitioner or clinical investigator (depending on the local organization of the participating hospital) will be responsible for the pre-operative and post-operative data collection. The surgeon who performed the ALND will be responsible for the peri-operative data collection. Data will be stored anonymously under a unique trial number. The principal investigators (EL and PG) will have access to the data. All data will be collected in an online case report form and an online participant questionnaire (PQ). The timetable and source of the data collection is listed in Table 1.

**Table 1 T1:** Data collection

**Data**	**Source**	**Pre-operative**	**Peri-operative**	**Follow-up at 6, 12, and 24 months**
Baseline characteristics	CRF	x		
Medical history	CRF	x		
Pre-operative tumor status/markers	CRF	x		
Operation data including:	CRF		x	
Registration				
Randomization				
Post-operative complications	CRF/PQ	x^a^		x
Quality of life	PQ			x
Axillary recurrence rate	CRF			x

CRF, case report form; PQ, participant questionnaire.

^a^The volume, circumference and mobility of the arm will be measured pre-operatively.

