### Statistics

#### Sample size

The clinically relevant amount of lymphedema is stated as a volume difference of 200 ml or more between both arms. Primary research shows that the risk of BCRL is 15% in patients undergoing an ALND. It is expected that ARM-ALND will reduce the risk to 5%. Based on these assumptions, we will need to study 140 subjects in the standard ALND group and 140 subjects in the ALND-ARM group to be able to reject the null hypothesis that the failure rates for experimental and control subjects are equal with a probability (power) of 0.8. The Type I error probability associated with this test of the null hypothesis is 0.05.

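### The primary endpoint classifies lymphedema from the post-operative arm difference alone and leaves out the pre-operative difference that the trial measures

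*Protocol article*

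**What the plan says.** - **Case definition** (Primary and secondary outcome measures): "Lymphedema is defined as a difference in limb volume of greater than 200 ml between the treated and untreated side". The threshold is referred to a cited study.
- **Same threshold in the Sample size section**: "The clinically relevant amount of lymphedema is stated as a volume difference of 200 ml or more between both arms". This has no pre-operative term either, and it includes the value 200 ml, which the first definition excludes.
- **Measurement**: the sentence before the case definition reads "Both upper limbs will be measured pre-operatively and post-operatively". The footnote to Table 1 (Data collection) adds: "The volume, circumference and mobility of the arm will be measured pre-operatively".
- **Target of the trial** (Abstract, Methods/design): "Primary outcome is the presence of axillary surgery-related lymphedema".
- **Primary test** (Data analysis): an uncorrected chi-square test on the proportion with lymphedema, with 24 months as the primary time point. Baseline values are named as a covariate only in the ANCOVA of continuous outcomes such as pain and quality of life.
- **Eligibility** (Participants): no criterion concerns arms that already differ before surgery.

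**The concern.** The stated outcome is lymphedema related to axillary surgery, but one post-operative comparison of the two arms cannot separate what surgery caused from what was there before. Two examples show errors in both directions, reading the difference as treated minus untreated:

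- The treated arm is 150 ml larger before surgery and swells by 51 ml. The difference is 150 + 51 = 201 ml, so the patient is a case.
- The treated arm is 100 ml smaller before surgery and swells by 290 ml. The difference is −100 + 290 = 190 ml, so the patient is not a case.

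This affects the primary endpoint of a trial planned at 80% power, although the information needed to correct it is already collected.

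**Working it through.** **1. The plan's own figure.** Inputs from the Sample size section: 15% v 5%, power 0.80, alpha 0.05, 140 per group. The test is the uncorrected chi-square (Data analysis). Sidedness is not stated; two-sided is assumed here because it reproduces the number. With the pooled-variance formula and mean rate 0.10:

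n = [1.960 × √(2 × 0.10 × 0.90) + 0.842 × √(0.15 × 0.85 + 0.05 × 0.95)]² / 0.10² = 140.1 per group, or 141 rounded up.

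Power at 140 per group is 0.7997. The plan's figure reproduces.

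**2. If 15% and 5% are rates of change-based swelling (assumption).** Let f be the share of patients without true swelling who are classified as cases, and Se the share of true cases still detected. The observed rate is p × Se + (1 − p) × f. The documents give neither f nor Se.

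| Se | f | Observed rates | Difference (points) | Risk ratio | Power at 140 per group |
|---|---|---|---|---|---|
| 1 | 0 | 15.0% v 5.0% | 10.0 | 0.33 | 0.80 |
| 1 | 1% | 15.9% v 6.0% | 9.9 | 0.38 | 0.76 |
| 1 | 2% | 16.7% v 6.9% | 9.8 | 0.41 | 0.72 |
| 1 | 5% | 19.3% v 9.8% | 9.5 | 0.51 | 0.62 |
| 0.9 | 2% | 15.2% v 6.4% | 8.8 | 0.42 | 0.66 |

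Example for f = 2%: 0.15 + 0.85 × 0.02 = 0.167 and 0.05 + 0.95 × 0.02 = 0.069.

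**3. Same reading, different model.** Let the change be normal with SD 80 to 120 ml, with means set so that 15% and 5% exceed 200 ml. Add an independent normal pre-operative asymmetry with mean 0 and SD 50 to 100 ml (all assumed). The uncorrected definition then gives an absolute difference of 10.5 to 11.0 points, a risk ratio of 0.38 to 0.59 and power of 0.78 to 0.60. The absolute difference does not shrink here. The risk ratio still moves toward 1 and power still falls, because both rates rise.

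**4. If 15% and 5% are rates of the uncorrected definition.** Power under the plan is 0.80, as in step 1. What a change-based endpoint would do depends on the model:

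- With Se = 1, the corrected rate is (p − f)/(1 − f). For f = 1% this gives 14.1% v 4.0% and power 0.84. For f = 2% it gives 13.3% v 3.1% and power 0.88.
- In the normal model, keeping 200 ml as the cut-off for change lowers the rates. With SD of change 100 ml and asymmetry SD 50 ml, the SD of the post-operative difference is √(100² + 50²) = 111.8 ml, and the change-based rates are 12.3% v 3.3%, power 0.81. With SDs of 80 and 100 ml they are 4.9% v 0.4%, power 0.64. Over the grid in step 3, power runs from 0.64 to 0.81.

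A change-based endpoint can therefore gain or lose power at the same cut-off.

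**The case against.** **The plan has lost power.** A reader might infer that the trial falls below 80%, or that the sample size is wrong. The documents do not support this. The Sample size section states the inter-arm threshold first and then says "Primary research shows that the risk of BCRL is 15% in patients undergoing an ALND", with 5% expected under ARM-ALND. The natural reading attaches both rates to the uncorrected difference, and the planned power then stands. The losses in steps 2 and 3 require the other reading and assumed asymmetry.

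**The treatment effect shrinks.** A reader might also infer this without qualification. It holds for the risk ratio. The absolute difference falls only slightly when no cases are masked (Se = 1), falls more when some are, and does not fall in the normal model.

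**Validity is intact.** This stands. Misclassification unrelated to the allocated group leaves the type I error unchanged and favours neither arm.

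**Baseline is used elsewhere.** The Data analysis section plans a repeated-measures analysis of changes in continuous data, linked to the expectation of earlier and more severe lymphedema, and this may well cover arm volume. It does not alter the binary primary endpoint.

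**The detail may sit elsewhere.** The definition follows a cited study that cannot be checked here, and the article condenses a longer protocol. However, this is not a detail left unstated: the article gives the threshold in two sections, and neither has a pre-operative term. A citation for the threshold is no reason to leave out a baseline that this trial collects.

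**Conclusion.** The point holds as an improvement to the primary endpoint that needs no new data, not as a demonstrated power error. The definition and the primary test use the post-operative difference alone, so pre-existing asymmetry is counted as, or can mask, the surgery-related swelling that the trial sets out to measure. The consequence is noise and a risk ratio drawn toward 1, without bias in favour of an arm. This rests on asymmetry being independent of allocation, which randomisation provides on average.

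Its size cannot be set from the documents. If 15% and 5% describe change-based swelling, power would be 0.76 to 0.62 for assumed f of 1% to 5% with no masked cases, and lower if some are masked. If they describe the uncorrected difference, power is 0.80 as planned.

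**What to change.** Choose one of two routes and fix it before outcomes are seen, because choosing between definitions afterwards would be data-driven.

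1. Define primary lymphedema as the treated-minus-untreated volume difference at 24 months, minus the same difference before surgery, exceeding the 200 ml threshold. Keep the uncorrected definition as a sensitivity analysis, for comparison with the cited study.
2. Keep the cited definition as primary, but adjust the 24-month comparison for the pre-operative inter-arm volume difference, for example by logistic regression in place of the unadjusted chi-square. Add the change-based definition as a sensitivity analysis.

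Handle the circumference and abduction criteria in the same way, provided that both sides are recorded before surgery; the Table 1 footnote speaks only of the arm. Reconcile the two thresholds, since one section excludes exactly 200 ml and the other includes it. State which definition the 15% and 5% refer to.

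Costs: no new measurement of volume is needed, but route 1 changes the primary endpoint. The planning rates may not carry over, and the event rate may be lower, so the sample size should be rechecked. A second pair of volumes adds measurement error. Patients without a pre-operative volume cannot be classified under the change-based definition, so the plan must say how they are handled. Route 2 leaves the endpoint and its planning rates as they are, but also needs a rule for a missing pre-operative volume.
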